### Participants

An urban secondary school in the city of Madrid (Spain) that was previously known to the authors expressed interest in being involved in research and agreed to participate. Students enrolled in levels 3º ESO (usually aged 14 to 15 years old) and 4º ESO (usually aged 15 to 16 years old) were targeted, given that early to mid-adolescence is a key time for the emergence of common mental health disorders [29]. Participants came from 3 classes at level 3º ESO and 2 classes at level 4º ESO (each class having around 30 students each). No incentives are being given to the adolescents or the school for participating in this project.

Parents or guardians, as well as adolescents, were provided with information about the study and were required to provide signed consent before Time 1 assessments. Participants and families were informed that (1) responses to the questionnaires will be keep confidential; (2) they will be able to withdraw from the study at any time; (3) participants receiving the preventive intervention will be taught specific skills that will help them to better cope with situations that provoke anxiety/depression both now and in the future; and (4) participants assigned to the WL control condition will receive the preventive intervention after the WL period. Inclusion criteria for participants were providing written, informed consent (both the adolescent and at least 1 parent or legal guardian) and being able to understand, write, and read Spanish. Spanish proficiency was determined based on teacher report. Due to the universal prevention goal of this study, there were no other exclusion criteria. Classes of students were randomly assigned either to the preventive intervention group or to the WL control group (see Figure 1). Time 1, Time 2, Time 3, and Time 4 assessments, as well as intervention sessions, are being conducted at the school during school hours.

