Power analyses were conducted using G*Power Version 3 software [67]. Sample size required to detect a Cohen *d* effect of .30 was estimated, based upon effect sizes reported in meta-analyses of school-based anxiety and depression preventive interventions conducted all over the world [68,69], including in Spain [70]. Calculations showed that with a power level of .80 and a significance level of alpha = .05, a total sample of N_Non-cluster_ of 74 was required to detect a significant effect. However, potential loss of power due to data clustering had to be considered in the sample size calculation. The impact of the ICC on the planned trial size depends on the so-called design effect, which can be calculated as 1+(*m*-1) ICC, with *m* referring to the number of participants recruited per cluster [66]. For this study, the ICC is unknown although, on the basis of prior school-based prevention research, the expected ICC for anxiety and depression-related outcomes is approximately 0.02 [27]. The anticipated average class (cluster) size for this study is 27 students meeting inclusion criteria, resulting in a design effect of 1.52. The design effect is then multiplied by the previously calculated N_Non-cluster_ [66], resulting in an estimated sample size for this trial of 112, considering the design effect. In addition, we estimated a dropout rate of 10% based on previous studies [65,71], resulting in an estimated total sample size of 123 (at least 62 students in each group). The total number of clusters required can be calculated dividing the estimated total sample size by the estimated number of participants recruited per cluster (123/27), resulting in 4.56 clusters [66]. Therefore, to achieve a sample of this size, a total of 157 students and 5 clusters were recruited.

As the flow diagram shows (Figure 1), the final number of participants matches these a priori computations closely: 90 students (10 lost at Time 2) were allocated to the preventive intervention group and 62 students (4 lost at Time 2) were assigned to the WL control group. In addition, this study will allow for calculation of the ICC and effect sizes for all primary and secondary outcomes, which could be very important in assisting future researchers in establishing the feasibility and ideal sample size for future full-scale cluster RCTs applying the UP-A as a preventive intervention.

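### Five classes of 27 cannot give at least 62 students in each group, and the 10% dropout allowance was added rather than divided out (minor, wording only)

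*Protocol article*

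**What the plan says.** The Sample Size section of the protocol article works in a chain:

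- The starting point is a total of 74 before clustering ("of 74 was required to detect a significant effect"), for a Cohen d of 0.30, "with a power level of .80 and a significance level of alpha = .05".
- For clustering it states that "the expected ICC for anxiety and depression-related outcomes is approximately 0.02". With an anticipated average of 27 eligible students per class, the design effect is 1.52 and the total becomes 112.
- A 10% dropout allowance follows, "resulting in an estimated total sample size of 123 (at least 62 students in each group".
- The number of classes is the total divided by the class size, "123/27), resulting in 4.56 clusters", and five classes were recruited, with 157 students.

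The section then reports 90 students allocated to the intervention (10 lost at Time 2) and 62 to the waitlist (4 lost at Time 2), and comments that "the final number of participants matches these a priori computations closely". The Participants section describes three classes at one school level and two at the other, "each class having around 30 students each". The Randomization section says that classes were allocated 1:1, with near-equal numbers of classes per arm.

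**The concern.** The per-group minimum, the anticipated class size and the number of classes are all stated, and they cannot all hold. The class count comes from the overall total as if students could be divided freely between arms, but an arm can only be made of whole classes. With an odd number of classes, one arm must be smaller, and at the planned class size it falls below the stated minimum.

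The dropout step is a separate and smaller matter. Adding 10% to the required number does not restore that number once 10% are lost.

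At stake is the accuracy of the published planning figures, and of the sentence that measures recruitment against them. The conduct of the trial is not at issue.

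**Working it through.** **Inputs**, all from the Sample Size section unless noted: base total 74; ICC 0.02; 27 students per class; dropout 10%; allocation by class, 1:1 (Randomization section); allocated 90 and 62. The base of 74 is taken as given; whether it follows from d = 0.30 is a separate question.

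**The plan's own figures reproduce.**

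- Design effect: 1 + (27 - 1) x 0.02 = 1.52
- With clustering: 74 x 1.52 = 112.48, stated as 112
- With dropout: 112 x 1.10 = 123.2, stated as 123
- Per group: 123/2 = 61.5, stated as at least 62
- Classes: 123/27 = 4.56, taken as 5

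**Class count by arm (main point).**

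- Most even split of five classes: 3:2
- Arm sizes at 27 per class: 3 x 27 = 81 and 2 x 27 = 54
- Shortfall in the smaller arm: 62 - 54 = 8, and 8/62 = 13%
- Classes needed for 62 in one arm: 62/27 = 2.30, so 3 per arm, 6 in all
- Class size at which two classes reach 62: 62/2 = 31

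**Dropout (secondary point).**

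- What 123 leaves after 10% loss: 123 x 0.90 = 110.7, below 112
- Dividing out the loss: 112/0.90 = 124.4, so 125, or 63 per group after rounding 62.5 up. Starting from the unrounded 112.48 gives 124.98, also 125.
- Effect on classes: 125/27 = 4.63, still 5

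**Does the uneven split cost power?** For arms of size a and b, the equal-arm total with the same precision is 4ab/(a + b).

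| Arms | Calculation | Equal-arm total |
|---|---|---|
| Planned, 81 v 54 | 4 x 81 x 54/135 | 129.6 |
| Allocated, 90 v 62 | 4 x 90 x 62/152 | 146.8 |
| After Time 2 losses, 80 v 58 | 4 x 80 x 58/138 | 134.5 |

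The first two exceed both 123 and 125. The third is a number after losses, so it is compared with 112, and it exceeds that. Five full classes hold 5 x 27 = 135 students, which more than covers the imbalance.

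**Realised class sizes.** The flow diagram is not available here, so a 3:2 split with the intervention in three classes is inferred from 90 and 62 students and classes of about 30. It gives 90/3 = 30 and 62/2 = 31 per class.

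**The case against.** The strongest reply is that nothing went wrong. The figure of 27 was only an anticipated average, and larger classes contradict nothing. The waitlist arm started with 62, exactly the stated minimum. After Time 2 it had 58, above the 112/2 = 56 per arm that should remain after dropout. The dropout correction moves the total by 2 students (1.6%) and leaves the class count at five. Each stated number also follows from the steps the authors chose, so this is not a slip of calculation. All of that stands, and it is why the point is minor.

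It does not remove the inconsistency at planning. With the article's own 27 per class, the five-class rule does not secure its own per-group minimum; the minimum was reached because the waitlist classes averaged 31.

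A reader might go further in four ways that the article does not support:

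- **That the trial is short of students or power because of these steps.** On the article's own base figure it is not, as the equal-arm totals show.
- **That the claimed match is false for the waitlist arm.** That arm met 62 at allocation, and is one student below the corrected 63. The visible departure is upward: 90 in the intervention arm and 152 in total.
- **That the design effect should be recomputed at the realised class size.** The sentence on the match compares recruitment with the calculation made in advance, which used 27.
- **That the article offers this method as a template for later trials.** What it offers future researchers is the ICC and effect sizes.

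**Conclusion.** The point holds as a minor inconsistency in the stated planning figures. The main part is the class count: 27 per class, five classes and at least 62 per group are incompatible, and the smaller arm would be expected to hold 54, a gap of 8 students. The secondary part is the dropout step, which should give 125 (63 per group) where the article has 123. The two are independent, since correcting the dropout step leaves five classes and so does not change the 81 v 54 split.

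The incompatibility of the class count follows from the article's figures alone. The statement that power is not reduced is narrower: it takes the base of 74, the ICC of 0.02 and the single design effect of 1.52 as the article gives them, and says nothing about whether those inputs are sound.

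**What to change.** Change the wording of the Sample Size section in three places:

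1. Give the total after dropout as 112/0.90 = 125, or 63 per group.
2. After the class count, state that five classes of 27 imply an expected 81 and 54 students, not 62 or 63 in each group. Add that three classes per arm would be needed to reach the per-group figure at that class size, and that 81 v 54 is equivalent to about 130 students in equal arms, so the total is still sufficient on the stated base figure.
3. Replace the sentence on the close match with the numbers: 63 planned per arm, 90 and 62 allocated. Note that the waitlist arm reached 62 because its classes averaged 31.

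The cost is a few sentences, and the planning figures look slightly less tidy. Enrolment and analysis do not change.

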### Randomization

#### Sequence Generation and Allocation Concealment

Each participating class (cluster) was randomly allocated 1:1 to the preventive intervention or WL control condition. We used a balanced design, resulting in about the same number of classes in each of the preventive intervention and WL control groups (Figure 1). No matching, blocking, or stratification took place. Cluster randomization was undertaken for the ecological validity of providing the intervention at the class level. The randomization was conducted by a researcher not involved in the current project by using a computer random number generator. Random assignment occurred before Time 1 measurements took place because the Research Ethics Committee that provided ethical approval for this study requested that the Informed Consent forms signed by parents/guardians and participants state whether the student was going to be in the experimental or the WL control group.

#### Implementation and Blinding

The adolescents complete all questionnaires using Qualtrics Survey software in a designated classroom, and a research assistant is available to provide assistance if necessary and to ensure independent responding. The research assistant is blind to the allocated treatment group at time of completing questionnaires to reduce risk of bias. Blinding of participants at the cluster or individual level is not possible for the ethical reasons explained above. Regardless, blinding participants at the cluster or the individual level after baseline would have been impossible due to the nature of the experimental intervention, which requires active participation from the preventive intervention group compared to no involvement or participation from the WL control group in the first phase of the study. An attention-control intervention would have been ideal but was beyond the scope of this study.

## Results

Analysis and presentation of data will be in accordance with CONSORT guidelines and, in particular, the extension to cluster randomized trials [28]. Statistical significance will be considered as a *P* value of less than .05, and statistical analysis will be mainly carried out using IBM Statistical Package for the Social Sciences, Version 24.0 (IBM SPSS). Data will be analyzed taking the clustering of students within classes into account.

To check for possible differences at pre-intervention between intervention and WL control groups, a chi-square test for nonparametric variables and a 2-tailed *t* test for continuous variables will be performed at the student-level and class-level on sociodemographic variables as well as on primary and secondary outcome measures. Complete case analyses (excluding participants with missing data), intent-to-treat analyses (including all randomized individuals), and completer status analyses (ie, participants that achieved completer status, that is, participants that attended to 7 or more sessions), will be conducted according to the initial allocation of classes to either preventive intervention or WL control groups. Results will be reported at cluster and individual levels, including information about the estimated effect size and its precision, as well as ICCs for each primary and secondary outcome.

In relation to missing data, we will follow the guidelines for analyzing and reporting cluster RCTs with missing data established by Fiero and et al [72] and Díaz and et al [73]. Specifically, we will (1) attempt to follow up on all randomized clusters and individuals in order to limit the extent of missing data; (2) report the number of clusters and individuals lost to follow-up, as well as numbers of missing values for each variable of interest, which will be important when deciding what analysis to use; (3) collect and report information about reasons for losses to follow-up and other missing values, which may help when deciding the plausibility of the missing-at-random assumption; (4) justify the choice of principal analysis, the missing data mechanism assumed, and the plausibility of these assumptions; (5) perform and report sensitivity analyses to explore the robustness of the trial results to departures from the missing data assumption made in the primary analysis; and (6) follow the CONSORT extension for cluster trials [28] to ensure comprehensive reporting and transparency of methods used. To investigate the potential effects of missing data, the baseline characteristics of the adolescents will be compared for those with and without missing data.

The effectiveness of the intervention will be assessed using complex samples procedures in SPSS as well as multi-level (or hierarchical) modeling that includes both fixed (intervention effects) and random (students in classrooms) effects. Experimental and WL control groups will be compared at 3 points in time: Time 1 (pre-treatment), Time 2 (post-treatment for intervention group), and Time 3 (3-month follow-up for intervention group). In addition, within-participant analyses will be conducted only with the WL control group at Time 4. ICCs will be calculated for all primary and secondary outcomes to compare the variation due to school class and the total variance.

Secondary analyses will include (1) repeating the primary analysis adjusting for any variables exhibiting significant imbalance at baseline to assess whether this influences the findings; (2) examining intervention changes for adolescents who scored above the clinical cut-off for anxiety and/or depression at Time 1; (3) investigating potential predictors of intervention effects including all participants (both intervention and WL control groups) after the WL receives UP-A; (4) comparing observed and expected attrition rates, as well as observed and expected ICCs; and (5) analyzing answers to checklists completed by group leaders.

At the time of submitting this manuscript, all participants have been recruited and we have conducted Time 1 and Time 2 assessments with the experimental and WL control groups. The experimental group has also completed the preventive intervention. We expect the WL control group to complete the preventive intervention and Time 4 assessments in July 2017.

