We predict that the UP-A preventive intervention group will exhibit greater improvement on all primary and secondary outcome measures at post-intervention and follow-up compared to the WL control group. We also expect that WL participants will experience significant improvements on all outcome measures after receiving the intervention. Greater improvement in the primary and secondary outcome variables is expected in those with higher levels of home practice, more frequent practice of a greater number of strategies outside session, higher levels of engagement and effort during sessions, more sessions attended, greater knowledge of core program contents after the intervention, and greater interest in psychology. In relation to age and gender as predictors, earlier studies have shown contradictory results [27] and therefore no hypothesis was forwarded in this regard. We also hypothesize that results will support the feasibility of school-based implementation of UP-A in a prevention group format, as evidenced by a number of participants achieving treatment completer status (attending at least 7 out of the 9 sessions), as well as the acceptability of the intervention, as evidenced by participants’ self-rated satisfaction at post-intervention.

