#### Revised Child Anxiety and Depression Scale-30

The Revised Child Anxiety and Depression Scale-30 (RCADS-30) [32] is a widely-used questionnaire measuring self-reported anxiety and depressive symptoms in children and adolescents. The scale is comprised of the following subscales derived from the Diagnostic and Statistical Manual of Mental Disorders, 4th edition (DSM-IV) criteria: (1) social phobia, (2) generalized anxiety disorder, (3) obsessive-compulsive disorder, (4) panic disorder, (5) separation anxiety disorder, and (6) major depressive disorder. The 6 subscales are summed to create a Total Anxiety and Depression score. Each item is scored from 0 (“Never”) to 3 (“Always”), with higher scores representing more severe symptoms. The RCADS-30 has demonstrated good psychometric properties with normative and clinical populations [33,34]. In the current sample, the 6 individual subscales have demonstrated adequate to good internal consistency both at Time 1 (alpha .70 to .85) and at Time 2 (alpha .72 to .86). The Total Anxiety and Depression scale has demonstrated excellent internal consistency at Time 1 (alpha = .92) and at Time 2 (alpha = .93) assessments.

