## Discussion

### Principal Findings

This paper describes the study protocol of a cluster RCT testing the first adaptation of the UP-A as a school-based anxiety and depression preventive intervention. The primary outcomes are change in anxiety and depression symptoms. Secondary outcomes include change in participant-identified top problems ratings, conduct problems, hyperactivity/inattention symptoms, peer problems, prosocial behavior, school grades, depression and anxiety-related interference, positive and negative affect, anxiety sensitivity, emotional avoidance, life satisfaction, quality of life, self-esteem, school adjustment, and discipline problems. This study will also improve our understanding of factors that might influence the effectiveness of UP-A through the preliminary examination of a number of potential predictors of treatment outcomes, including age, gender, number of sessions attended, engagement and effort during sessions, understanding of basic program concepts, adherence to home practice, and practice of specific strategies outside of sessions.

This study focuses on a school-based, universal prevention program for anxiety and depression, which has the advantage of being easily integrated into a school curriculum and thereby limiting the extent to which participants are segregated from peers and at risk for possible stigmatization due to their participation [74]. It is surprising that, despite the high co-occurrence between anxiety and depression and their shared risk and vulnerability factors, preventive interventions have typically focused on either depression or on anxiety alone [10]. For instance, of the 30 total studies included in a meta-analysis conducted by Ahlen and colleagues, 13 studies focused primarily on depression prevention, 10 studies focused primarily on anxiety prevention, and only 7 studies focused on prevention of both disorders [27]. A transdiagnostic approach to preventing anxiety and depression may enhance the efficacy, generalizability, and cost-effectiveness of prevention programs [10], as well as prevent the development of related emotional disorders.

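### Three primary scales share one unadjusted .05 level, and the article names neither a single primary scale nor how many results must be significant

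*Protocol article*

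**What the plan says.** The Discussion (Principal Findings) defines the primary outcomes as constructs: "The primary outcomes are change in anxiety and depression symptoms". Under Primary Outcome Measures these become three instruments: RCADS-30, CDN for depression and EAN for anxiety. For RCADS-30, "The 6 subscales are summed to create a Total Anxiety and Depression score", so both the total and the subscales are available for testing. No instrument is ranked above another.

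The Results section compares the groups at Times 1, 2 and 3, which gives two comparisons after baseline. Study Aims predicts that the intervention group will "exhibit greater improvement on all primary and secondary outcome measures at post-intervention and follow-up compared to the WL control group". The same section makes maintenance at 3 months a separate fourth aim.

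The error level appears twice: the criterion in Results, "Statistical significance will be considered as a *P* value of less than .05", and the Sample Size calculation, "with a power level of .80 and a significance level of alpha = .05". Neither mentions more than one primary test. Two-sided testing is stated only for the baseline checks ("a 2-tailed *t* test for continuous variables will be performed").

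**The concern.** Anxiety is measured by RCADS-30 and EAN, and depression by RCADS-30 and CDN. With overlapping primary scales, one .05 level and no success rule, whichever scale comes out significant can be presented as meeting the primary aim. A reader who sees .05 would then overestimate how strongly the primary conclusion is protected against chance.

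The timing adds to this. The article reports that Time 2 data had been collected and gives Time 2 internal consistencies for all three scales. A choice of primary scale left open at that stage could be made after seeing results. According to the abstract, data analysis was still to come, in the second semester of 2017, so the gap could be closed before the comparison.

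**Working it through.** **The plan's own figure.** The Sample Size section says "Sample size required to detect a Cohen *d* effect of .30 was estimated" and that "a total sample of N_Non-cluster_ of 74 was required to detect a significant effect". That 74 reproduces for one repeated-measures group-by-time F test at alpha .05, with f = d/2 = 0.15, 2 groups and 3 measurements. A within-person correlation of 0.5 and sphericity are my assumptions.

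- Noncentrality = N × 3 × f² / (1 − 0.5) = 74 × 3 × 0.0225 / 0.5 = 9.99, on 2 and 144 degrees of freedom.
- Power is 0.806 at N = 74 and 0.795 at N = 72.
- Then 74 × 1.52 = 112.5, taken as 112, and 112 × 1.10 = 123.2, taken as 123.

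A plain two-group comparison at d = 0.30 would need about 350 in total, so 74 does not come from that test. I use the reproduction only to show that the size rests on one test at .05.

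**Number of primary tests.** The article allows two counts:

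- Three: one group-by-time test per scale, or Time 2 alone.
- Six: 3 scales × 2 post-baseline times.

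**Chance of at least one false positive when any one counts.** For k independent tests this is 1 − 0.95^k: 1 − 0.95³ = 14.3% and 1 − 0.95⁶ = 26.5%. For correlated tests I used simulated two-sided z tests, 400,000 draws per setting. The article gives no correlations, so they are assumed, here common to all tests:

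| Assumed correlation | Three tests | Six tests |
|---|---|---|
| 0 | 14.3% | 26.5% |
| 0.3 | 13.6% | 24.1% |
| 0.5 | 12.6% | 20.8% |
| 0.6 | 11.8% | 18.7% |
| 0.7 | 10.8% | 16.4% |
| 0.8 | 9.8% | 14.0% |

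With separate between-scale and between-time correlations, each from 0.5 to 0.8, six tests give 14.9% to 21.9%.

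**If every test must be significant.** The rate cannot exceed 5%. It was below 1% in every six-test setting run.

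**Cost of correcting.** Under the same repeated-measures model, the N needed before clustering at the Bonferroni level is:

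- Three tests, .05/3 = .0167: 96, so 96 × 1.52 × 1.10 = 160.5, about 161 students. Power at N = 74 is 0.66.
- Six tests, .05/6 = .0083: 110, so 110 × 1.52 × 1.10 = 183.9, about 184 students. Power at N = 74 is 0.57.

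The article reports 152 students randomized.

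**The case against.** The strongest reply is that this is silence in a journal article. Multiplicity is usual SAP content, and a general significance convention does not rule out a later correction. That is fair as far as the correction goes. It does not cover the choice of primary outcome, which belongs in the protocol. Here the article itself fixes three overlapping primary scales and one level.

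A reader might infer that the plan declares any single significant result a success, or that its error rate simply is 16-26%. The documents support neither. No success rule is given, and that range needs six tests, an any-one-wins rule and correlations from 0 to about 0.7. The top end needs independence, which is implausible for scales of overlapping symptoms in the same students. Nor does the article claim familywise control that is then broken.

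It would also be too strong to say that nothing is ordered. Maintenance at 3 months is a separate aim, and the 3 × 2 repeated-measures design permits one test per scale. The ordering is missing among the scales. For time it is only unsettled, because Study Aims also predicts superiority on the primary measures at follow-up.

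The opposite inference, that the prediction on all measures means all must succeed, does not hold either. It covers every secondary outcome too, so it reads as a hypothesis and not as a success rule.

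Finally, the study calls itself preliminary and commits to reporting effect sizes with their precision. Both points lessen the harm, but the trial still sets out to test effectiveness on a primary aim.

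**Conclusion.** The concern holds in conditional form. The article leaves the primary scale and the success rule open while applying .05 throughout. On an any-one-wins reading, the chance of a false primary result is about 10-14% with three tests and about 14-26% with six. Even the lowest figure, 9.8%, is about twice .05.

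These figures assume two-sided tests, correlations between 0 and 0.8, and that each test holds its own 5% level. They cover multiplicity across scales and times only. Six may be too few: the primary aim also includes preventing clinically elevated levels, the RCADS-30 subscales could be tested, and three analysis sets and two modelling approaches are planned. I put no rate on those.

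**What to change.** Before any between-group analysis, choose and record one of these:

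1. **One primary outcome.** Name the RCADS-30 Total Anxiety and Depression score at Time 2, tested at .05. Make CDN and EAN at Time 2 key secondary outcomes with Holm correction (smaller P against .025, the other against .05).
2. **Three primary scales.** Keep RCADS-30 total, CDN and EAN at Time 2 with Holm correction (ordered P values against .0167, .025 and .05, stopping at the first that fails).

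In both cases, make Time 3 the maintenance question of the fourth aim. State that the choice was made after Time 2 data collection but before comparative analysis. If the groups have already been compared, the choice cannot be presented as made in advance.

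The reason to prefer the RCADS-30 total is that it covers both constructs. Internal consistency does not separate it from EAN (alpha .92 and .93 against .91 and .94 at Times 1 and 2).

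The change is to the wording of the plan, plus the disclosure. Option 1 needs no multiplicity allowance for the primary test, but CDN and EAN lose stand-alone primary status. Only one of the six subscales measures depression, so the total leans towards anxiety. Option 2 keeps both constructs visible but lowers power per scale; the Bonferroni figures above show the loss at its first step. Whether secondary outcomes may carry significance claims at all is a matter of preference, and this point does not depend on it.

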**Methods:**

A cluster, randomized, WL, controlled trial design with classroom as the unit of randomization was used in this study. Five classes including a total of 152 adolescents were randomized to the experimental or WL control groups. Participants in the experimental group received 9 55-minute sessions delivered by advanced doctoral and masters students in clinical psychology. The WL control group will receive the intervention once the 3-month follow-up assessment is completed.

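### Effectiveness is to be tested on five classes with SPSS Complex Samples, whose ordinary form has about 11% type I error at nominal 5%, and the plan does not say whether it or the multilevel model decides

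*Protocol article*

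**What the plan says.** The Abstract (Methods) gives the number of randomised units: "Five classes including a total of 152 adolescents were randomized to the experimental or WL control groups". Sample Size gives the split by student: "90 students (10 lost at Time 2) were allocated to the preventive intervention group and 62 students (4 lost at Time 2"). Participants describes "each class having around 30 students each", so 90 and 62 students correspond to three and two classes. That split is inferred, because the flow diagram is not shown. Under Sequence Generation and Allocation Concealment the article states: "No matching, blocking, or stratification took place".

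In the Results section the significance threshold is a P "value of less than .05, and statistical analysis will be mainly carried out using IBM Statistical Package for the Social Sciences, Version 24.0". The effectiveness sentence is: "The effectiveness of the intervention will be assessed using complex samples procedures in SPSS as well as multi-level (or hierarchical) modeling" and the multilevel model is one "that includes both fixed (intervention effects) and random (students in classrooms) effects". No reference distribution or degrees-of-freedom method is given for either procedure, and neither is named as the one that decides. The Study Design section describes a three-time by two-group repeated measures layout.

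**The concern.** The Complex Samples procedures estimate the variance by linearisation, that is, from the spread of class totals about their arm mean. This estimator relies on many sampling units. With three and two units per arm it is biased downwards, and its df are set by the number of units, not by what is left after two arm means have been estimated. A small ICC does not help, because the fault lies in having five units.

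A multilevel model can also be too liberal with five classes if its test is referred to a normal or student-level distribution.

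The article states that clustering is allowed for, so readers will take the P values and intervals for the primary aim at face value. If one procedure is significant and the other is not, the plan gives no rule.

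**Working it through.** **Inputs from the article.** Five classes; 90 v 62 students, hence 3 v 2 classes; about 30 per class; expected ICC 0.02; d = 0.30; alpha 0.05; power 0.80.

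**Assumptions.** Class is the sampling unit; two-sided test; one post-intervention score; normal data; equal classes of 30.

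**The plan's own figures.** The unclustered total of 74 is reproduced by a repeated-measures interaction with f = 0.30/2 = 0.15, two groups, three times and an assumed correlation of 0.5. Then 74 × 1.52 = 112.48; 112 × 1.10 = 123.2; 123/27 = 4.56 clusters. The chain applies a design effect but makes no allowance for having only five clusters.

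**Complex Samples, one stratum.** Let s² be the variance of a class mean.
- True variance of the arm difference: (1/3 + 1/2)s² = 0.833s².
- Linearised estimator: 5/4 × (sum of squared class deviations/9 in the three-class arm + the same/4 in the two-class arm).
- Its expectation: 5/4 × (2/9 + 1/4)s² = 0.590s².
- Ratio: 0.590/0.833 = 0.708, an underestimate of about 29%. The s² cancels, so the ICC plays no part.
- Reference df: 5 − 1 = 4 (critical value 2.776), although only 5 − 2 = 3 remain (3.182).

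**Complex Samples, arm as stratum.** The factors become 3/2 and 2, giving 3/2 × 2/9 + 2 × 1/4 = 1/3 + 1/2, which is unbiased, on 3 df.

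**Multilevel model.** With equal classes, REML reproduces the class-level variance when the class component is estimated above zero, and pools to student level when it is estimated as zero. Satterthwaite df are then 3 and 148 respectively.

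**Type I error (%) under no effect**, 200,000 simulated trials per ICC:

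| ICC | 0 | 0.01 | 0.02 | 0.05 | 0.10 |
|---|---|---|---|---|---|
| Complex Samples, one stratum, 4 df | 10.8 | 10.7 | 10.8 | 10.9 | 10.7 |
| Complex Samples, arm as stratum, 3 df | 5.8 | 5.7 | 5.8 | 5.8 | 5.8 |
| Multilevel, normal reference | 4.0 | 5.8 | 7.3 | 10.6 | 12.6 |
| Multilevel, Satterthwaite df | 3.1 | 4.1 | 4.9 | 5.8 | 5.7 |
| Either row 1 or row 4 significant | 11.1 | 11.0 | 11.2 | 11.3 | 11.0 |
| Class-level t test, 3 df | 5.1 | 5.0 | 5.1 | 5.0 | 5.0 |
| Class variance estimated as zero | 60 | 48 | 40 | 24 | 12 |

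Runs with classes of 30/30/30 v 31/31, and with the Time 2 completers (80 v 58), gave similar rates; the normal-reference figure at ICC 0.02 lay between 7.1% and 7.7%.

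**Group-by-time contrast (conditional).** If the random effects are class and student intercepts only, the class effect cancels from a change over time and the contrast is tested at student level. With an ICC of change of 0.02 the ignored design effect is 1 + 29 × 0.02 = 1.58. A nominal 1.96 then acts as 1.96/√1.58 = 1.56, a two-sided error of about 12%.

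**Power of the class-level test.** At ICC 0.02, SE = √[(0.02 + 0.98/30) × 0.833] = 0.2095 SD and the noncentrality is 0.30/0.2095 = 1.43. On 3 df this gives about 18% power. With an assumed baseline correlation of 0.5, SE = 0.2095 × √0.75 = 0.181 and power is about 22%.

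**The case against.** The article does not give the Complex Samples set-up. Declaring arm as a stratum brings the error to about 5.8%, and the statement that no stratification took place concerns randomisation, not the software's design file. This stands: 10.8% belongs to the ordinary one-stratum form and is not certain to be what will be run.

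A condensed article may leave the df method to an analysis plan that is not shown. This also stands, so the missing df method for the multilevel model is not in itself the fault. The fault is a named procedure unsuited to five units, with no lead analysis named beside it.

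A reader might infer that both procedures double the false-positive rate. The figures do not support that. At the expected ICC of 0.02 the multilevel model gives about 7.3% with large-sample inference and about 5% with Satterthwaite df; it doubles only near ICC 0.05, and only with large-sample inference. A reader might also infer that the group-by-time test will certainly be run at student level, with 12% error or, at an ICC of change of 0.05, about 21%. The article neither sets out the full random-effects structure nor gives an ICC of change, so this is only a possibility.

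Finally, the Results section commits to the CONSORT cluster extension, to reporting at cluster and individual levels, and to justifying a principal analysis. This suggests that one lead analysis is intended. It does not identify that analysis or make linearised inference valid with five classes.

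**Conclusion.** The point holds in a limited form. Complex Samples in its ordinary unstratified form on 3 v 2 classes has about 10.8% type I error at any ICC; this rests on the inferred 3:2 split, class as sampling unit and 4 df. The multilevel model at ICC 0.02 lies between about 5% and 7.3%, depending on a df choice that the article does not fix, and could be worse for the group-by-time contrast if no class-by-time effect is fitted. With no rule on which procedure decides, accepting either gives about 11% even when the multilevel test uses Satterthwaite df, so a well-run multilevel model does not rescue the plan. The Limitations section mentions 152 adolescents in five classes as a moderate sample size but does not address the validity of the tests.

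**What to change.** Drop Complex Samples for inference and name one lead analysis, with confidence intervals on the same df as the test. Either of these would serve:
- A class-level analysis: regress the student outcome on baseline without arm, then compare the five class mean residuals by a t test on 3 df.
- A multilevel model with Satterthwaite or Kenward-Roger df, using a class-by-time random effect or a baseline-adjusted outcome at a single time. State beforehand how df are set when the class variance is estimated as zero, which happens in about 40% of trials at ICC 0.02. Holding them at 3 in that case makes the test very conservative (about 0.7% error).

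A permutation test is no substitute at the 5% level: with 10 possible 3:2 allocations its smallest P is 1/10.

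The change is a matter of analysis wording and one simple analysis. The real cost is precision. Without baseline adjustment the 95% half-width at ICC 0.02 is 3.182 × 0.2095 = 0.67 SD, and power for d = 0.30 is about 18% (about 22% with an assumed baseline correlation of 0.5), against the stated 80%. Recruitment is complete, so the stated power should be restated rather than the sample enlarged.
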